## Abstract

**Introduction::**

Post-operative cognitive dysfunction (POCD) is frequent in patients older than 60 years undergoing major non-cardiac surgery, and increases both morbidity and mortality. Anesthetic drugs may exert neurotoxic effects and contribute to the genesis of POCD. The hypothesis of the POCD-ELA trial was that closed-loop target-controlled infusion of propofol and remifentanil could reduce the occurrence of POCD by decreasing the risk of excessive depth of anesthesia and the dose of anesthetic drugs.

**Methods and analysis::**

We designed a single-center, single-blind, randomized, controlled, parallel trial and aim to include 204 patients aged >60 years undergoing elective major non-cardiac surgery. Patients will be randomized to receive closed-loop versus manual target-controlled infusion of propofol and remifentanil guided by bispectral index monitoring. Cognitive assessment will be performed the day before surgery (baseline) and within 72 hours after surgery, using a battery of validated neuropsychological tests. The primary outcome is the incidence of POCD within 72 hours after surgery. POCD is defined as a Z-score value > 1.96 for at least 2 different tests or a Z-score composite value >1.96. The calculation of the Z-score is based on data from an age-matched control population who did not undergo surgery or general anesthesia.

**Ethics and dissemination::**

This study was approved by the Ethics Committee (Comité de Protection des Personnes Est-II) and authorized by the French Health Products Agency (Agence Nationale de Sécurité des Médicaments, Saint-Denis, France). The University Hospital of Besancon is the trial sponsor and the holder of all data and publication rights. Results of the study will be submitted for publication in a peer-review international medical journal and for presentation in abstract (oral or poster) in international peer-reviewed congresses.

**Registration::**

The trial is registered with ClinicalTrials.gov (Identifier: NCT02841423, principal investigator: [name], date of registration: July 22, 2016). Last amendment of protocol: version 8.0 April 2018.

Strengths and limitations of this studyThis is the first study to investigate whether closed-loop anesthesia could decrease the rate of early post-operative cognitive dysfunctionSingle-blind randomized controlled trial.The definition of post-operative cognitive dysfunction is based on an alteration of cognitive performance compared to an age-matched control population who did not undergo surgery or anesthesiaSingle-center studyNo long term cognitive assessment, however early POCD is a relevant surrogate endpoint for long term cognitive impairment.

## Background

1

Post-operative cognitive dysfunction (POCD) is a common complication that has been reported to occur in 26% of patients aged 60 years or over, up to 7 days after major non-cardiac surgery.^[1]^ POCD is usually defined as a significant alteration of cognitive function (especially memory and executive functions) during the postoperative period, compared to age- and disease-matched controls.^[1–3]^ Early POCD has been associated with increased mortality,^[4,5]^ a higher rate of dementia and premature departure from the workforce.^[5]^ Several factors have been reported to be related to POCD, but the underlying pathogenic mechanisms are complex and not fully understood.^[6]^

In particular, animal experiments have suggested that general anesthetics may exert neurotoxic effects that could lead to POCD.^[7–9]^ Since no specific treatment for POCD has been identified, prevention remains the only therapeutic measure available. In this context, anesthesia appears as a potentially modifiable contributor to POCD in the perioperative period.^[10]^ Chan et al reported that anesthesia guided by bispectral index (BIS) monitoring could decrease POCD by reducing the dose of anesthetic drugs.^[11]^ Recently, lighter anesthesia targeting higher BIS values was associated with a lower rate of POCD after total knee replacement.^[12]^ However, these data remain controversial.^[13,14]^ The discrepancies observed among the different studies could be partially explained by the difficulty in accurately maintaining the BIS value within the target range of 40 to 60 with manual titration of the anesthetic drugs. Closed-loop target-controlled infusion of propofol and remifentanil has been shown to improve the time spent within the BIS target range and to decrease both the number and the length of episodes of excessive depth of anesthesia (BIS value < 40).^[15–17]^

The hypothesis of the POCD-ELA trial was that closed-loop target-controlled infusion of propofol and remifentanil could lower the occurrence of POCD by decreasing the risk of excessive depth of anesthesia.^[18]^

## Objectives

2

The POCD-ELA study was designed to assess whether closed-loop compared to manual target-controlled infusion of propofol and remifentanil guided by BIS monitoring could decrease the incidence of postoperative cognitive dysfunction in patients undergoing major non-cardiac surgery.

## Methods and design

3

This manuscript is written in accordance with the SPIRIT guidelines for the reporting of interventional trial protocols.^[19]^

### Trial design

3.1

The POCD-ELA trial is a prospective randomized, controlled, single-blind, single center study.

POCD-ELA is a sub-study of the ELA (ClinicalTrials.gov Identifier: NCT01198639) study, which aimed to assess whether closed-loop propofol-remifentanil administration compared to manual target-controlled infusion could improve 1-year mortality after non-cardiac surgery.

### Eligibility

3.2

Adult patients scheduled for major non-cardiac surgery expected to last more than 1 hour and performed under general anesthesia are eligible for inclusion. Inclusion and exclusion criteria for the present study are detailed below. Patients undergoing emergency surgery are excluded due to the impossibility of implementing organizational aspects of the protocol in emergency conditions (see below). Patients undergoing cardiac surgery are also excluded since POCD has specific underlying mechanisms in this population.

### Inclusion criteria

3.3

Signed informed consentAge 50 to 85 years (inclusive)American Society of Anesthesiologists’ (ASA) physical status I to IIIAbility to speak, write and understand French languageScheduled non-cardiac surgery lasting more than 1 hourSurgically sterilized or menopausal women for at least 24 months; or, among non-menopausal women, use of an effective method of contraception.Patient affiliated to French Social Security or equivalent.

### Exclusion criteria

3.4

ASA physical status IV or higherPatients unable to speak, write or understand FrenchPresence of a pacemakerScheduled brain or cephalic surgeryDiagnosed dementia (Alzheimer's disease, Lewy body dementia), cerebral or psychiatric pathology (tumor, stroke with sequelae, Parkinson's disease, severe depression or psychosis), as well as those receiving antipsychotic treatment (antidepressants, neuroleptics, long-term benzodiazepines, antiparkinsonian drugs)General anesthesia within 1 year before inclusion, except for diagnostic proceduresContraindication to propofol or remifentanil administrationLegal incapacity or limited legal capacitySubjects without health insurancePregnant or breast-feeding womenSubjects within the exclusion period of another study.

### Study outline

3.5

Eligible patients are screened during the anesthesia consultation and receive all information relating to the study by phone before hospital admission. Written informed consent is obtained the day before surgery by investigators after oral explanation of the study before inclusion. After written informed consent is obtained, patients are randomized.

After randomization, a first cognitive assessment is performed by a neuropsychologist blinded to the treatment allocation, using a battery of validated neuropsychological tests (see below).

Patient characteristics, past medical history including ASA physical status, and preoperative blood glucose, sodium, potassium and creatinine levels are collected. The prescription of oral premedication is at the discretion of the anesthesiologist in charge of the patient; any treatment prescribed is also recorded.

On arrival in the operating room, standard monitoring (General Electric Healthcare) is put in place. A dedicated indwelling venous catheter is inserted in a forearm vein and connected to an infusion pump via a 3-way Smartsite (Alaris Medical Systems, San Diego, CA), with a priming volume of 0.3 ml. The BIS electrode (Zipprep, Covidien, Mansfield, MA) is positioned on the patient's forehead and connected to either an A-2000 XP (version 3.11) BIS monitor (Covidien) or a BIS Module (version 4.0 XP, GE-Healthcare, Helsinki, Finland). All patients receive intravenous anesthesia with a medical device enabling calculation of effect-site concentrations of anesthetics. A standard computer is used to provide a user interface and to control communication with the BIS monitor and with both propofol and remifentanil infusion pumps (Alaris) via an RS232 serial port (Infusion Toolbox 95w version 4.11 software (Department of Computer Science, Faculty of Medicine, Université Libre de Bruxelles, Brussels)). The protocol for general anesthesia depends on the treatment allocated by randomization, that is, closed-loop (intervention group) or manual (conventional group) target-controlled infusion of propofol and remifentanil guided by BIS monitoring (see below). With the exception of propofol and remifentanil delivery, the anesthetic protocol is at the discretion of the anesthesiologist in charge of the patient.

Surgical and anesthetic details are recorded, including: type and duration of surgery; intraoperative blood loss and urine output, blood transfusion, total volume of fluids infused; type and total dose of drugs administered; and all blood pressure, heart rate and pulse oximetry values measured from induction of anesthesia to discharge from the operating room. All data concerning BIS monitoring and propofol and remifentanil delivery are extracted from the computer connected to the BIS monitor and to the propofol and remifentanil infusion pumps. Post-operative pain management and assessment is recorded.

A second cognitive assessment is performed by a neuropsychologist blinded to the treatment allocation within 72 hours after the end of surgery, using the same battery of validated neuropsychological tests as during the first evaluation (see below). If the patient refuses to participate in the second cognitive assessment, the consent is considered to be withdrawn, and the patient is excluded from the study.

### Randomization, allocation concealment and blinding

3.6

Centralized randomization is performed using a specialised website on the day before surgery. A computer-generated permuted-block randomization list with varying block sizes (ratio 1:1, block size of 2 and 4) was implemented on the website at the beginning of the ELA-study by an independent data manager. The block size is unknown to the investigators. The investigator enters data online regarding each patient to enable inclusion, and the treatment randomly assigned to the patient is immediately provided to the investigator by the website. The allocation ratio is 2:1 (interventional: conventional groups), and the randomization is stratified by age (> or <70 years) and cancer (yes/no). The allocation ratio and the stratification are the same as in the ELA study.

Patients and outcome assessors (neuropsychologists) are blinded to the treatment allocated.

### Study procedure and interventions

3.7

In the interventional group, anesthesia is performed using a dual closed-loop controller allowing automated propofol–remifentanil titration guided by BIS. A computer plays the role of an interface between the BIS monitor and the propofol and remifentanil infusion pumps (Alaris Medical, Hampshire, UK) via an RS232 serial port (Infusion Toolbox 95w version 4.11 software). Propofol and remifentanil are automatically titrated by the controller to maintain a BIS value as close as possible to 50 and between 40 and 60 (target range).^[15,20]^ The BIS electrode impedance is checked regularly, and the BIS sampling rate is 256 Hz with a 15 s smoothing rate. The BIS value is considered valid when the signal quality index is >50. The clinical effectiveness and safety of the closed-loop controller have previously been published elsewhere.^[15]^

In the conventional group, propofol and remifentanil are manually titrated by the anesthesiologist and the nurse anesthesiologist in charge of the patient to maintain a BIS value within the target range. In the conventional group, the BIS monitor and the propofol and remifentanil infusion pumps are also connected to the computer to allow data collection regarding the management of anesthesia with the same precision as in the interventional group.

Intraoperative ketamine is forbidden in the 2 groups to avoid biased estimation of the depth of anesthesia by BIS monitoring.

### Outcome measures

3.8

The primary outcome is the incidence of POCD within 72 hours after major non-cardiac surgery under general anesthesia. A cognitive assessment is performed the day before surgery (baseline) and within 72 hours after surgery using a battery of validated neuropsychological tests (see below) during a face-to-face interview with a trained neuropsychologist. To avoid potential underestimation of the cognitive status, the evaluation is conducted in a quiet environment, after checking for the absence of uncontrolled pain, hypoglycemia, or dysnatremia. The cognitive assessment includes 7 neuropsychological tests that explore 6 different cognitive domains:1.the global cognitive functioning using the Mini-Mental State Examination (MMSE)^[21]^ and the Mattis Dementia Rating Scale,^[22]^2.attention, using the Trail Making Test, part A (TMT-A),3.executive function, using the Trail Making Test, part B (TMT-B) and Stroop tests,4.verbal fluency, using the Isaacs Set Test (IST),^[23]^5.learning and episodic verbal memory, using the Memory Impairment Screen (MIS) test,^[24,25]^6.a psychomotor task using the crossing-off test.^[26]^

According to the method described by Moller et al,^[1,3]^ a Z-score value will be calculated for each neuropsychological test as follows: Z-score = (X1–X2)/SD; where X1 and X2 are the score values obtained at baseline and at the 2^nd^ assessment respectively; and Standard deviation (SD) is the SD of the test performed in an age-matched control population who did not undergo surgery or general anesthesia. The SD observed in the control population is known for all tests used. A composite Z-score value will be calculated as the mean of the Z-scores of all tests.

POCD is defined as a Z-score value >1.96 for at least 2 different tests or a Z-score composite value >1.96.

Secondary outcomes are the differences in the score obtained on each test between baseline and post-surgery assessment.

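### The POCD Z-score takes baseline minus second assessment for every test with no sign reversal, so where a higher score is worse, as in completion times, decline cannot count towards POCD and improvement can

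*Protocol article*

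**What the plan says.** Section 3.8 (Outcome measures) of the protocol article defines the primary endpoint in three steps.

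- **Z-score.** "a Z-score value will be calculated for each neuropsychological test as follows: Z-score = (X1–X2)/SD". The terms are defined: "X1 and X2 are the score values obtained at baseline and at the" second assessment respectively, and SD comes from an age-matched control population without surgery or general anesthesia.
- **Composite.** "A composite Z-score value will be calculated as the mean of the Z-scores of all tests".
- **Classification.** "POCD is defined as a Z-score value >1.96 for at least 2 different tests or a Z-score composite value >1.96".

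The battery named in the same section is MMSE, Mattis, TMT-A, TMT-B, Stroop, Isaacs Set Test, MIS and crossing-off. Executive function is covered by "executive function, using the Trail Making Test, part B (TMT-B) and Stroop tests" in the article's list, and the last domain is "a psychomotor task using the crossing-off test". The scored variable (time, errors, number correct) is not given for any test. Nowhere does the article say that the sign is changed for some tests, or that a positive Z means deterioration.

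**The concern.** Baseline minus second assessment is positive when the score falls. That marks decline only on tests where higher is better, which is the usual scoring of MMSE, Mattis, Isaacs and MIS. The Trail Making Tests are ordinarily scored as completion time, so a patient who becomes slower has a larger X2 and a negative Z. The threshold is positive only, so such a patient can never reach it on that test, while one who becomes faster can.

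This rule sets the primary endpoint and therefore every POCD count in the trial. TMT-B measures executive function, as does Stroop, and the Background (section 1) names executive function, with memory, as especially affected in POCD. At stake are missed cases, some false cases, and a loss of power, since the 26% and 10% used for the sample size must refer to deterioration.

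**Working it through.** **1. The planned sample size.** Inputs from section 3.11: 26% conventional, 10% interventional, two-sided alpha 0.05, power 80%, loss 5%, arms of 68 and 136.

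The pooled proportion at 1:2 is (0.26 + 2 × 0.10)/3 = 0.1533. The conventional-arm size is

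[1.96 × √(1.5 × 0.1533 × 0.8467) + 0.842 × √(0.26 × 0.74 + 0.10 × 0.90/2)]² / 0.16² ≈ 63.5, so 64.

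Then 64/0.95 = 67.4, so 68; 2 × 68 = 136; total 204. The plan's figure is reproduced. After 5% loss, 68 × 0.95 = 64.6 and 136 × 0.95 = 129.2, that is about 65 and 129 patients, with power about 81%.

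**2. The sign, test by test.** This is algebra on the printed formula.

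| Change between assessments | Z as written | Counts towards POCD? |
|---|---|---|
| Higher-is-better test, 2.5 SD worse | +2.5 | yes |
| Timed test, 2.5 SD slower | −2.5 | no |
| Timed test, 2.5 SD faster | +2.5 | yes |

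A patient 2.5 SD faster on both TMT-A and TMT-B, and otherwise unchanged, has two values above 1.96 and is labelled POCD. A patient 2.5 SD slower on both is not. This takes the two parts as different tests, as the list of domains does. Section 3.8 speaks of 7 tests but names 8, so if the two parts were counted as one test, a further reversed test would be needed.

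**3. The composite.** Suppose a patient is worse by d on all 8 scores and r of them are reversed. The composite is d × (8 − 2r)/8. With d = 2.5 the correctly signed value is 2.50. As written it is 2.5 × 4/8 = 1.25 for r = 2, 2.5 × 2/8 = 0.63 for r = 3, and 0 for r = 4. All are below 1.96. This patient would still be classified through the two-test criterion, by the tests that are not reversed.

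**4. Effect on rates and power.** The article gives no data for this, so the following is illustrative. Assumptions: 8 scores, each Z with unit SD, equal correlation between scores, and decline calibrated so that the correctly signed rule gives 26% and 10%. Power is for the Pearson test at 65 and 129, starting from about 81%.

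*Every patient shifted by the same mean decline (about 0.8 SD against 0.4 SD), correlation 0.1 to 0.4:*

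| Scores reversed | Power |
|---|---|
| 2 | about 65-72% |
| 3 | about 54-65% |
| 4 | about 41-54% |

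With 3 reversed, the observed rates would be about 13-16% against 5-6%.

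*Only a subset of patients declines, on all tests, with 3 reversed and correlation 0.1 to 0.3:*

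| Decline in the subset | Power |
|---|---|
| 1.5 SD | 63-68% |
| 2 SD | 74-75% |
| 2.5 SD | 80% |

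**5. Which error dominates.** With 3 reversed, a uniform mean decline of 0.5 SD and correlation 0.2 to 0.4, 42-51% of the correctly signed POCD cases are missed. The opposite error, POCD by the written rule only, affects about 0.2% of patients in that setting, and 0.7-0.9% if there is no mean decline.

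**The case against.** The strongest reply is that the premise lies outside the article. It speaks only of score values, and that a higher TMT score is worse is convention. For Stroop and crossing-off the direction depends on which score is taken. This stands as a limit on how many tests are affected, and it is why the range is 2 to 4.

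A second reply is that the formula is introduced as a published method, which may set the sign, and that the article condenses a longer protocol. The overall idea of POCD as impaired cognition is also clear from the Background. These make it plausible that the analysts would orient the scores correctly. They do not cure the text: the article writes out a formula with defined terms, applies it to each test, and adds a one-directional threshold. A correction that is not written down is not prespecified, and the direction for Stroop and crossing-off could then be chosen after the data are seen.

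Several stronger readings are tempting but not supported:

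- **That the trial will in fact misclassify patients.** The article shows only what follows if the rule is applied literally.
- **That slowing on a timed test cancels decline elsewhere in general.** This is true of the composite only. Under the two-test criterion the negative value simply fails to count, and the other tests can still trigger POCD.
- **That attention is among the functions the Background singles out.** It names memory and executive functions. Memory is tested by the MIS, which as usually scored is not affected.
- **That a large loss of power is established.** It ranges from large to almost none depending on the pattern of decline. A decline confined to the reversed tests would be worse than the cases shown.
- **That one arm is favoured.** The same rule applies to both arms, and patients and assessors are blinded.

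**Conclusion.** The point holds. As printed, the primary-endpoint rule gives the wrong sign for any score where higher is worse, and nothing in the article corrects it. That conclusion is algebraic and needs only one outside premise: that at least TMT-A and TMT-B are scored by completion time. Whether Stroop and crossing-off are also affected cannot be settled from the article.

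The size is uncertain. The power ranges shown rest on assumed correlations, unit SDs and an assumed pattern of decline, none of which the article supplies, so they indicate what could be lost and are not an estimate for this trial. Under those assumptions missed cases far outnumber false ones. Because the rule defines the primary endpoint and is cheap to repair, it should be corrected before the analysis.

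**What to change.** State in section 3.8, and in the analysis plan, that Z is signed so that a positive value always means deterioration:

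- (X1 − X2)/SD where a higher score is better;
- (X2 − X1)/SD where a higher score is worse.

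Add a small table giving, for each test, the scored variable and its direction, with Stroop and crossing-off settled explicitly. Let the same table show which scores make up the 7 tests, because this decides both the two-test criterion and the divisor of the composite. Apply the signs before counting tests and before averaging.

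The cost is one sentence and a table. No new data are needed, since the rule works on the two scores already recorded for each test, and the sample size stays at 204 because its 26% and 10% then refer to deterioration. The change should be recorded before outcomes are compared by arm.

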### Sample size calculation

3.11

The difference in primary outcome between groups will be compared using Pearson's Chi-squared test, based on an intention-to-treat analysis. Based on the data from the ISPOCD1 study,^[1]^ the expected rate of POCD in the conventional group is 26%. We assume that the expected rate of POCD in the interventional group (closed-loop infusion of propofol and remifentanil) is 10%. Considering a loss to follow-up rate of 5%, a total sample size of 204 patients was calculated (68 patients in the conventional arm, 136 patients in the interventional arm), on a final analysis using the Pearson's Chi-squared test (2-sided, power 80%, alpha 0.05) using the SAS software, version 9.4 (SAS Institute, Inc.).

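### The composite limb of the POCD definition cuts an unscaled mean of Z-scores at 1.96, so it adds almost nothing to the two-test rule

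*Protocol article*

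**What the plan says.** Section 3.8 (Outcome measures) gives the per-test score as "Z-score = (X1–X2)/SD; where X1 and X2 are the score values obtained at baseline and at the 2^nd^ assessment respectively". The SD is that of the test in an age-matched control population without surgery or anesthesia. On these SDs the article says: "The SD observed in the control population is known for all tests used". It then says: "A composite Z-score value will be calculated as the mean of the Z-scores of all tests". The endpoint follows: "POCD is defined as a Z-score value >1.96 for at least 2 different tests or a Z-score composite value >1.96". The Methods and analysis part of the Abstract repeats the same rule.

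No passage gives an SD for the composite or says that the mean is divided by one. On the size of the battery, section 3.8 states: "The cognitive assessment includes 7 neuropsychological tests that explore 6 different cognitive domains". The list that follows holds eight scores if Trail Making parts A and B are scored separately: MMSE, Mattis, TMT-A, TMT-B, Stroop, Isaacs, MIS and crossing-off.

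**The concern.** The value 1.96 marks the upper 2.5% of a score with mean 0 and SD 1. Each test Z is scaled towards that standard; the composite is not. Averaging shrinks the spread, so the same cut is far stricter for the mean than for a single test. A patient whose mean exceeds 1.96 will then nearly always have two tests above 1.96 already.

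The two limbs are joined by an or, so the second has a function only if it catches patients whom the first misses. The natural candidates are patients who decline moderately on many tests without a large fall on any two. If the limb cannot reach them, the primary endpoint is narrower than its wording suggests. The patient most able to qualify on the composite alone is one with a single extreme score, which is the case a two-test requirement would be expected to screen out.

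**Working it through.** **Inputs.** From section 3.8: plain mean, cut 1.96 for both limbs, 7 tests stated and 8 scores listed (both used below). Assumed, because the documents are silent: all scores oriented so that positive means decline, SD 1, normal, equal pairwise correlation c from 0.1 to 0.5.

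**The plan's own figure.** Section 3.11 plans for POCD rates of 26% v 10%, allocation 1:2, two-sided alpha 0.05 and power 80%. The pooled rate is (0.26 + 2×0.10)/3 = 0.1533. The conventional arm needs [1.96×√(1.5×0.1533×0.8467) + 0.8416×√(0.26×0.74 + 0.10×0.90/2)]² / 0.16² = 63.5, so 64. Then 64/0.95 = 67.4, so 68, and 68 + 136 = 204. The sample size reproduces and is not in question here.

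**SD of the mean.** For k scores, SD = √(c + (1−c)/k). It equals 1 only if c = 1.

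| c | SD, k=7 | share above 1.96 | SD, k=8 | share above 1.96 |
|---|---|---|---|---|
| 0.1 | 0.478 | 0.002% | 0.461 | 0.001% |
| 0.2 | 0.561 | 0.024% | 0.548 | 0.017% |
| 0.3 | 0.632 | 0.097% | 0.622 | 0.082% |
| 0.5 | 0.756 | 0.48% | 0.750 | 0.45% |

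The shares are for patients with no decline; a unit-SD score would give 2.5%. With k = 8 the cut lies 1.96/0.461 = 4.3 to 1.96/0.750 = 2.6 SDs out.

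**What the limb adds.** A mean above 1.96 needs a sum above 1.96k. If all other tests are at 0, one test must exceed 13.7 (k = 7) or 15.7 (k = 8). If the others are all at 1.0, it must exceed 7.7 or 8.7. Otherwise nearly all the remaining tests must sit just under 1.96.

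In simulations of at least one million patients per setting (k = 7 and 8, uniform decline 0 to 0.9 SD), the composite was met without the two-test rule in at most 22 per million, and mostly in 10 or fewer. With heavy-tailed scores (t with 3 df, k = 7) the figure was 0.05% to 0.12%. With a per-test SD of 0.63 or 1.41 in place of 1 it was at most 40 per million.

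**Effect of rescaling.** Cutting the mean at 1.96 times its own SD, and keeping the two-test rule, gives for 8 scores:

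| c | no decline: written | no decline: rescaled | uniform 0.6 SD decline: written | uniform 0.6 SD decline: rescaled |
|---|---|---|---|---|
| 0.1 | 2.3% | 3.8% | 16% | 29% |
| 0.2 | 3.0% | 4.1% | 17% | 24% |
| 0.3 | 3.5% | 4.3% | 17% | 21% |
| 0.5 | 4.3% | 4.6% | 17% | 18% |

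**Power.** Assume that 60% of conventional and 20% of interventional patients decline, 64 and 128 are analysed, and there are 8 scores. If decline is a uniform 1.0 SD, power for the written v rescaled rule is 0.71 v 0.84 at c = 0.2 and 0.57 v 0.59 at c = 0.5. If decline is 1.5 SD on 3 of the 8 scores, it is about 0.60 for both at c = 0.2, 0.57 v 0.56 at c = 0.3 and 0.53 v 0.53 at c = 0.5.

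**The case against.** The strongest reply is that little harm follows. The two-test rule is prespecified, is applied alike in both arms, and is scored by neuropsychologists blinded to allocation (section 3.6), so no bias between arms is shown. That stands.

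Three stronger readings are tempting, and the documents do not support them.

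- A reader might infer that the flaw costs power. It does so only when decline is diffuse and correlation is low. Rescaling also adds chance positives, and with decline confined to a few tests there is no gain.
- A reader might infer that the endpoint is moved away from the 26% on which the sample size rests. That depends on how the cited study scaled its composite, which the documents do not say.
- A reader might infer that the stated 7 tests is a miscount. It is correct if the two Trail Making parts are one test. What is open is how they count.

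It can also be said that section 3.8 follows a cited method, which may rescale. But that reference introduces the per-test Z, and the composite has its own explicit formula. Finally, the control SD may be that of a score and not of a change. That would alter the tail percentages above, but not the redundancy, as the runs with SD 0.63 and 1.41 show.

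**Conclusion.** The point holds as a defect in a stated rule. As written, the composite limb is almost never met unless the two-test rule already is, so POCD is in effect the two-test rule, and diffuse moderate decline counts only when it happens to carry two tests past 1.96. The redundancy holds over every setting examined. The number of patients affected does not have one value: for a uniform 0.6 SD decline on 8 scores, the gap between the written and the rescaled rule runs from 13 percentage points at c = 0.1 to 1 point at c = 0.5. These sizes rest on an assumed correlation and an assumed pattern of decline. The planned total of 204 is unaffected, and no error in the treatment comparison is shown.

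**What to change.** Before unblinding, and by protocol amendment, define the composite as the mean (or sum) of the Z-scores divided by the SD of that same mean (or sum) in the control population, and apply 1.96 to the result. If control data on the whole battery in the same people are not available, drop the composite limb and state that POCD is the two-test rule. In either case, state how many scores enter and whether TMT-A and TMT-B are one test or two, since this sets the denominator and decides whether the two parts together can satisfy the two-test rule.

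The cost is more than wording. It changes the primary endpoint definition of a trial that has been including patients since February 2013 and whose protocol is at version 8.0. It needs joint control data for one extra constant, whereas section 3.8 claims only the SD of each test. It also admits slightly more chance positives, for example 4.1% instead of 3.0% with 8 scores at c = 0.2. Dropping the limb avoids the last two costs and changes the classification of almost no patient.
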